## Statistical analysis

### Sample size

Based on a literature search of previous studies on hysterectomy rate after EA, we found variation in hysterectomy rates between 9 and 17.5% [3, 23–26]. An assessment in the Dutch population of hysterectomy rates after EA indicates a hysterectomy rate around 15% after previous EA in daily practice. For the sample size calculation, we assume a 15% hysterectomy rate after treatment with EA alone.

Based on a literature search on treatment with EA and LNG-IUS, we found two recently published studies with a comparable study population [15, 27]. These studies show hysterectomy rates after combined treatment between 0 and 11%. Therefore, in this study the hysterectomy rate in the group treated with EA and LNG-IUS is hypothesized to be 8% [15, 27]. Using an alpha of 0.05 and a beta of 0.2 and the 15% hysterectomy rate in the EA alone group and 8% in the EA + LNG-IUS group, 646 participants are needed to achieve 80% power. This enables the detection of a 7-percentage point’s difference between the group proportions. The sample size was calculated using the two-sided Z-Test with unpooled variance. Assuming a 10% loss-to-follow-up rate, we need to recruit 718 participants in the trial (359 per group). This sample size calculation was performed using PASS15.0.10.

### Data-analysis

The primary analysis will evaluate if treatment of HMB by combined EA and LNG-IUS is superior to treatment by EA alone. The primary outcome measure will be a relative risk with 95% confidence interval and chi-squared test for hysterectomy at 24 months after treatment. The null-hypothesis is that combined endometrial ablation (EA) and LNG-IUS does not decrease the hysterectomy rate. The primary outcome will be analysed on the intention-to-treat population. Interim analyses will not be conducted.

Quality of life and longitudinal data on PBAC-scores will be analysed using Generalized Estimating Equations with treatment group, time, and treatment group—time interaction as variables, and a random effect for participants. Secondary outcomes that are dichotomous will be expressed as percentages and relative risks along with corresponding 95% confidence intervals. Calculating P-values will be based on the chi-square test or Fisher exact test, whichever is applicable. For continuous variables, the means will be presented along with the standard deviation, or the medians will be presented along with the interquartile range. Differences between the treatment groups will be estimated as differences in means of medians with t-test or Mann–Whitney test for inference (e.g. NRS-score pain). Questionnaires will be processed with the appropriate algorithms and presented by the usual methods (EQ5D and MMAS), with the baseline values adjusted for. Continuous data from questionnaires will be transformed or categorised as appropriate for the distribution of the data.

Quality-of-life data will be modelled using techniques that allow for missing data. Additional interventions or reinterventions can be obtained from medical files and will therefore have low rates of missing data. For remaining secondary outcomes measured using questionnaires, multiple imputation will be considered if necessary.

In addition to the analysis of the primary outcome on the intention-to-treatment population, the risk for hysterectomy will also be estimated for the per-protocol population.

The per-protocol population will evaluate all participants who have completed their treatment as randomised. Those who are randomised to endometrial ablation have undergone this treatment. Those who are randomised to endometrial ablation together with the placement of an LNG-IUS have this treatment and the IUS remained in situ for at least 6 months. P-values < 0.05 will be considered to indicate statistical significance. The analysis will be done using the software Statistical Package for the Social Sciences (SPSS, Inc., Chicago, IL, USA).

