### Participants recruitment, randomisation and collection of data

Participants meeting the eligibility criteria will be counselled about the study by their physician or a research nurse, who will provide them with written information about the study. Women will be counselled according to the ‘shared decision making’ principle. Women who agree to participate in the study must provide written informed consent before randomization can take place by a research nurse or researcher.

Randomisation will be stratified by the presence of pre-existing dysmenorrhoea at baseline (pain during menstruation for which most of the menstrual periods pain medication is necessary) and by age (under and above 45 years old). Variable block sizes of size 2, 4 and 6 will be used.

The online software tool Castor EDC (www.castoredc.com) will be used for randomisation, sending questionnaires, and data collection. The computer will randomly assign a unique numeric code for every subject, consisting of the hospital and the consecutive participant number. A coded data set will be handled, and only the local investigator and the research nurse on site will have access to the key (code to personal information linkage). These coded data are available to investigators, research staff, and quality assurance and monitoring personnel. After the study is complete, data will be archived for a period of 15 years. Personal data is handled in compliance with the EU General Data Protection Regulation and the Dutch Act on Implementing the General Data Protection Regulation.

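### The primary relative risk and chi-squared test do not use the dysmenorrhoea and age strata of the randomisation, which makes the analysis slightly conservative if those factors predict hysterectomy (minor)

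*Protocol article*

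**What the plan says.** The section on recruitment and randomisation sets two stratification factors: "Randomisation will be stratified by the presence of pre-existing dysmenorrhoea at baseline" "and by age (under and above 45 years old". That gives 2 × 2 = 4 strata. Allocation is in permuted blocks: "Variable block sizes of size 2, 4 and 6 will be used".

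The Data-analysis section then names the confirmatory analysis: "The primary outcome measure will be a relative risk with 95% confidence interval and chi-squared test for hysterectomy at 24 months after treatment". It is run on the intention-to-treat population, and no stratification factor or covariate is mentioned. The two factors come back only under Subgroup analysis, where interaction terms are tested in a generalised linear model. Adjustment for baseline is stated for the questionnaire scores but not for hysterectomy.

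The Sample size section also works without strata: "The sample size was calculated using the two-sided Z-Test with unpooled variance".

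**The concern.** Blocking within strata keeps the arms nearly equal on dysmenorrhoea and age group. If these factors are related to hysterectomy, the difference between arms varies less from trial to trial than it would under simple randomisation. The crude chi-squared test and the crude interval do not know this. Their variance still includes the between-stratum part that the design has removed.

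The consequences are a slightly wide interval, a test whose true type I error falls somewhat below the nominal 5%, and a small amount of power left unused. At stake is the efficiency of the one confirmatory comparison, and also clarity. If a stratified result is produced later beside the crude one, the plan should already say which of them is primary.

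**Working it through.** **1. The plan's own figure.** Inputs from the Sample size section: 15% v 8%, two-sided alpha 0.05, power 80%, unpooled variance.

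n per arm = (1.960 + 0.842)² × (0.15×0.85 + 0.08×0.92) / 0.07² = 7.849 × (0.1275 + 0.0736) / 0.0049 = 322.1, so 323 per arm and 646 in total. With 10% loss, 646/0.9 = 717.8, so 718 (359 per arm). Both stated figures reproduce. The chi-squared test uses the pooled variance, and its power at 323 per arm is 79.8% by formula. Sample size and stated analysis therefore agree: both are unadjusted.

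**2. Size of the crude test after stratified randomisation.** With overall risk p = 0.15, the crude test uses the total variance p(1−p) = 0.1275. With balanced strata, the variance that actually applies is the mean of pₛ(1−pₛ) over strata. Hence

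true type I error ≈ 2 × [1 − Φ(1.960 × √(total / within))].

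The documents give no stratum data. **Assumptions:** four equal strata, overall risk 15%, multiplicative risk ratios as listed.

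| Risk ratio, dysmenorrhoea / age | Stratum risks | Within-stratum variance | Within / total | Effective critical value | Type I error, formula | Type I error, simulated |
|---|---|---|---|---|---|---|
| 1 / 1 | 15% in all | 0.1275 | 1.000 | 1.960 | 5.0% | – |
| 2 / 1.5 | 8, 12, 16, 24% | 0.1240 | 0.973 | 1.987 | 4.7% | 4.5% |
| 3 / 2 | 5, 10, 15, 30% | 0.1188 | 0.931 | 2.031 | 4.2% | 4.2% |
| 4 / 2 | 4, 8, 16, 32% | 0.1160 | 0.910 | 2.055 | 4.0% | 4.0% |

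Example, last row: the mean of 0.0384, 0.0736, 0.1344 and 0.2176 is 0.1160, and 0.1160/0.1275 = 0.910. The crude standard error is too large by a factor of 1/√0.910 = 1.048, about 5%.

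The simulated column is from 40,000 trials of 646 women per setting with stratum-balanced allocation. The stratified test held 4.8 to 5.1% there. Over these three prognostic settings its power gain was 0.4 to 1.6 points (81.4% to 83.0% at 4/2).

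**3. Second simulation, with odds ratios and blocks of 2, 4 and 6** (40,000 trials of 646, equal strata, 15% v 8% for power):

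| Odds ratio, dysmenorrhoea / age | Type I error, crude v stratified | Power, crude v stratified |
|---|---|---|
| 1 / 1 | 5.0% v 5.1% | 80.4% v 80.3% |
| 1.5 / 1.5 | 4.8% v 5.0% | 80.5% v 80.6% |
| 2 / 2 | 4.7% v 5.0% | 80.5% v 81.0% |
| 3 / 2 | 4.4% v 5.0% | 80.8% v 81.7% |
| 3 / 3 | 4.1% v 4.9% | 81.3% v 82.7% |
| 5 / 3 | 3.9% v 5.0% | 81.9% v 83.9% |

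A further set of runs with risk ratios from 1/1 to 4/2 gave crude type I error from 5.1% down to 4.0% and a power gain of about 0 to 2.4 points. The approaches agree. The crude test's departure is downward only (values just above 5% are simulation noise), and its simulated power stays at or above 80% throughout.

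**The case against.** The strongest defence is that nothing in the named analysis is invalid. A crude intention-to-treat relative risk from 1:1 randomised arms estimates a well-defined marginal effect without bias. The trial was sized for an unadjusted test, so plan and sample size match.

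A reader might infer two stronger things: that the 5% error rate is breached, or that the trial falls short of its planned power. The documents and the figures support neither. The type I error moves below 5%, so false-positive risk does not rise. Simulated power of the crude test is at least 80% in every setting, and it increases as the strata become more prognostic. This part of the defence stands in full.

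It is also fair that the article never says why these two factors were chosen. Since both are planned subgroups, balance within subgroups could be the whole reason. The Background links dissatisfaction after ablation to bleeding and pain, which makes a role for dysmenorrhoea plausible. For age there is no such statement, and no stratum rate is given for either factor. A risk ratio of 4/2 implies an eightfold spread in risk that nothing in the article supports. This stands as well: the harm is conditional, and zero if the factors do not matter.

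Two further points carry less weight. A Mantel-Haenszel relative risk summarises the strata by one common ratio, while the subgroup analyses ask whether the effect differs by these same factors. That is a matter of interpretation, and it does not affect the validity of the Cochran-Mantel-Haenszel test of no effect. Lastly, a separate analysis plan could settle adjustment. But the article does not leave the method open: it names the estimate and the test, so the point concerns a stated choice and not a gap.

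**Conclusion.** The point holds as a minor one. The design stratifies by two factors and the stated primary analysis uses neither. If both predict hysterectomy, the crude interval is up to about 5% too wide on the log scale, the true type I error lies between about 4.0% and 5.0%, and about 0 to 2 points of power are forgone. This is for assumed risk ratios from 1/1 to 4/2 with four equal strata. At milder settings (odds ratios of 1.5/1.5 or 2/2) the gain is only 0.1 to 0.5 points.

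For scale, formula power rises from 79.8% at 323 per arm to 83.8% at 359 per arm. That is 4.0 points for 72 women, or about 0.056 points per woman. A gain of 0.4 to 1.6 points is thus worth roughly 7 to 29 women.

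No failure of error control, shortfall in planned power or bias follows from the documents. The case for change is that the improvement costs nothing: where the factors are irrelevant, the stratified test performs the same as the crude one within simulation error (80.3% v 80.4% power).

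**What to change.** State as the primary analysis of hysterectomy at 24 months one of these two, chosen before any outcome data are seen by arm:

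- a Mantel-Haenszel relative risk over the four randomisation strata with 95% confidence interval, tested by Cochran-Mantel-Haenszel; or
- a relative risk from modified Poisson regression (log link, robust variance) with treatment, dysmenorrhoea and age group as terms.

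Use the stratum values recorded at randomisation. Keep the crude relative risk and chi-squared test as a named supporting analysis, so that the result comparable with the sample size calculation is still reported. The subgroup interaction tests stay as they are.

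The cost is a few sentences in the analysis plan. Both factors are already recorded for every woman, no extra participants are needed, and 646/718 need not be recalculated. The plan already foresees a generalised linear model for the subgroups, so the regression option brings in no new class of method.

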## Methods/design

### Objective

The aim of this study is to assess whether the insertion of an LNG-IUS directly after EA is more effective in reducing the need for subsequent hysterectomy within two years of the EA in women with HMB and undergoing EA, as compared to EA alone. Also, the study will evaluate women’s satisfaction, reinterventions and complications, side effects, post-ablation menstrual bleeding patterns, quality of life, sick leave, and costs-effectiveness.

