### Outcome measures

The primary outcome will be the hysterectomy rate at two years after endometrial ablation as treatment for HMB. This will be measured using questionnaires in the follow-up period and checked by consulting the individual participant file. Secondary outcomes will include women’s satisfaction (on a 6-point Likert scale), condition-specific quality of life and general Quality of Life, severity of cyclical and non-cyclical pelvic pain, presence of (inter)menstrual bleeding, non-hysterectomy reintervention rates (removal LNG-IUS, medical or other surgical interventions), number and type of complications and adverse effects of treatment. Costs will be evaluated from a societal perspective. Outcomes will be collected via an online questionnaire completed by participants and via an online Case Report Form (CRF) completed by researchers.

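### The PBAC, menstrual-bleeding and cyclical-pain analyses take no account of hysterectomy; used as observed, they favour the arm with more hysterectomies

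*Protocol article*

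**What the plan says.** All from the Protocol article.

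- **Outcomes.** The Outcome measures section lists among the secondary outcomes "presence of (inter)menstrual bleeding, non-hysterectomy reintervention rates", together with severity of pelvic pain and quality of life.
- **Collection.** Under Questionnaires for participants, and in Table 1, PBAC, MMAS, EQ-5D-5L and the 0–10 cyclic pain score are collected at 6, 12 and 24 months. A one-month menstrual calendar is added at 24 months. No exception is made for women who no longer have a uterus.
- **Analysis.** Under Data-analysis, "Quality of life and longitudinal data on PBAC-scores will be analysed using Generalized Estimating Equations" with group, time and their interaction. Dichotomous secondary outcomes are compared by relative risk. The pain score is compared by t-test or Mann–Whitney test.
- **Missing data.** The same section plans methods that tolerate missing values for quality of life, and possible multiple imputation for the remaining questionnaire outcomes. Hysterectomy is not mentioned.
- **Expected event rates.** Under Sample size, "we assume a 15% hysterectomy rate after treatment with EA alone", against 8% in the combined arm.
- **Populations.** Intention-to-treat is named for the primary outcome only. The per-protocol analysis concerns hysterectomy risk only.

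**The concern.** The Abstract and the Discussion describe these hysterectomies as the result of persisting bleeding or pain, which is what the symptom outcomes measure. The event is common, is expected to be nearly twice as frequent in one arm, and removes the possibility of menstrual bleeding. Each route left open by the analysis text causes difficulty:

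- **Used as observed.** A woman whose ablation failed and who had a hysterectomy contributes a PBAC of zero and no menstrual bleeding.
- **Left blank.** The worst failures leave the comparison, more of them from the control arm. Their absence depends on the symptom being measured, which an ordinary unweighted GEE does not correct.
- **Imputed.** The model supplies menstrual bleeding for women who cannot menstruate.

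The better the LNG-IUS prevents hysterectomy, the more the as-observed bleeding result tilts against it. A choice of route made after the data are seen could move the result either way.

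**Working it through.** **1. The plan's own figure.** The plan says "646 participants are needed to achieve 80% power" and "The sample size was calculated using the two-sided Z-Test with unpooled variance". With 15% vs 8%, two-sided alpha 0.05 and power 80%:

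n per arm = (1.960 + 0.842)² × (0.15×0.85 + 0.08×0.92) / 0.07² = 322.1, rounded up to 323, so 646 in total. With 10% loss, 646/0.9 gives 718. Both figures reproduce, and nothing below changes them.

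**2. Expected hysterectomies by 24 months.** 323 × 0.15 ≈ 48 with EA alone; 323 × 0.08 ≈ 26 with EA + LNG-IUS.

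**3. Bleeding used as observed.** Let h be the hysterectomy rate and r the bleeding-free share among women who keep the uterus, equal in both arms. The document does not give r, so 30% to 70% is assumed.

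Bleeding-free share = h + (1 − h) × r

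| r | EA alone | EA + LNG-IUS | Spurious gain for EA alone |
|---|---|---|---|
| 30% | 40.5% | 35.6% | 4.9 points |
| 50% | 57.5% | 54.0% | 3.5 points |
| 70% | 74.5% | 72.4% | 2.1 points |

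Relative risk of bleeding, combined vs control = 0.92(1 − r) / [0.85(1 − r)] = 0.92/0.85 = 1.08. Since r cancels, this needs only the plan's two rates.

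**4. PBAC used as observed.** Arm mean = (1 − h) × mean among women with a uterus. That mean is not in the document; 20 to 100 is assumed, equal in both arms.

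- Mean 20: 17.0 (EA) vs 18.4 (EA + LNG-IUS), difference 1.4
- Mean 50: 42.5 vs 46.0, difference 3.5
- Mean 100: 85.0 vs 92.0, difference 7.0

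**5. How large a true benefit is hidden.** The two arms look equal when the relative risk of bleeding among women with a uterus is 0.85/0.92 = 0.924. A true relative reduction of about 7.6% is therefore cancelled. At r = 50% in controls, break-even in the combined arm is (0.575 − 0.08)/0.92 = 53.8% bleeding-free. A larger benefit still shows in the right direction, but reduced.

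**6. At 12 months.** The gap depends on how many hysterectomies have occurred by then, which is not given. If 50% to 67% have (assumption), the arms differ by 3.5 to 4.7 points in hysterectomy rather than 7, and the distortion shrinks in proportion.

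**7. Hysterectomy counted as non-response.** Success = (1 − h) × r.

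- r = 30%: 25.5% (EA) vs 27.6% (EA + LNG-IUS)
- r = 50%: 42.5% vs 46.0%
- r = 70%: 59.5% vs 64.4%

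The order reverses. With equal r, that difference comes entirely from the hysterectomy rates, so the composite partly repeats the primary outcome.

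**The case against.** **The article is silent, and a fuller document may hold the rule.** A reader might infer that the plan counts women with a hysterectomy as successes. It does not say so: no section states whether their values are used, blanked, imputed or scored as failure. A full protocol or SAP, not shown, could settle it. This bars any statement of what the plan will report. It does not remove the point, because the article does fix the instruments, time points, models and missing-data approach, and each route open under them handles this event badly.

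**The missing-data methods cover blank forms.** They do so formally. But a PBAC after hysterectomy is not an ordinary unobserved value, so those methods do not answer the problem. No size has been calculated for that route.

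**Quality of life.** A reader might extend the argument to it. The documents do not support that. The Discussion cites morbidity, psychological consequences and a median sick leave of 8.5 weeks after hysterectomy, so a best-possible score cannot be presumed. Quality of life after hysterectomy is real and well defined, and comparing it as observed is legitimate.

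**The bias is small and the calculation assumes no benefit in women with a uterus.** Both are correct. The Background expects the LNG-IUS to reduce persisting bleeding. If 40% of control women with a uterus are bleeding-free (assumption), the as-observed shares are 49.0% vs 44.8% when the combined arm is the same, z about 1.07 with 323 per arm. If the combined arm reaches 50%, they are 49% vs 54%, in its favour. A contradiction of the primary result should therefore not be forecast.

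**A composite is only one choice.** This also stands. As-observed results are defensible, and a worst-rank PBAC does not fit the planned GEE. The composite therefore belongs beside the as-observed analysis, not in its place.

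**Conclusion.** The point holds for menstrual bleeding and PBAC, and in principle for cyclical pain, where the documents allow no figure. The planned analyses ignore an event that is the primary outcome, is expected in 15% vs 8%, and ends menstrual bleeding. As-observed use gives a relative risk of bleeding of 1.08 against EA + LNG-IUS when bleeding in women with a uterus is equal. That rests on the plan's rates and on hysterectomy meaning no menstrual bleeding. The 4.9 to 2.1 points rest in addition on the assumed bleeding-free range of 30% to 70%. The effect is a modest attenuation, smaller at 12 months, and it reverses a true benefit only when the relative reduction in bleeding is below about 7.6%. The primary analysis and the sample size are not affected.

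**What to change.** Add a paragraph to Data-analysis, before outcomes are compared by arm:

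- For PBAC, menstrual bleeding and cyclical pain, state that values after hysterectomy are not treated as ordinary missing data.
- Beside the as-observed result, report a pre-specified composite analysis in which hysterectomy before the assessment counts as non-response. For PBAC and pain, use a dichotomised responder outcome or a rank test at each time point, outside the GEE.
- Leave EQ-5D-5L and other general quality of life as observed.

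Cost: a few extra secondary tables, and a composite that partly repeats the primary outcome and should be labelled so. The composite also needs to know whether hysterectomy came before each assessment. The article records reinterventions at set visits and checks hysterectomy against the participant file, but names no date field, so the date should be confirmed as collected or taken from that file. No additional participants are needed.

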#### Questionnaires for participants

Prior to treatment, participants will be asked to complete a baseline questionnaire containing a validated condition-specific quality of life measure Menorrhagia Multi-Attribute Scale (MMAS) as well as a validated EuroQol 5-level questionnaire [17–19]. The English language version of the MMAS questionnaire is shown in Additional file 1. Also, menstrual blood loss with a written Pictorial Blood Loss Assessment Chart (PBAC) score will be measured at baseline (Additional file 2) [20]. Participants will complete a questionnaire at six months follow-up asking about contraceptive use and smoking habits (Additional file 3). At 6-, 12- and 24-months participants will receive a questionnaire containing the MMAS questionnaire, the EQ-5D-5L questionnaire, and PBAC scoring, and questions on women’s satisfaction (6-point Likert scale), side effects of the LNG-IUS, and the presence of cyclic pelvic pain (pain score 0–10).

Societal costs (healthcare costs, lost productivity costs and informal care costs) are assessed using specifically adapted versions of the iMTA Productivity Cost Questionnaire (iPCQ) and the iMTA Medical Consumption Questionnaire (iMCQ) at 6, 12, 18 and 24 months (Additional file 4) [21, 22]. Participants will be asked to complete a menstrual calendar for one month to evaluate the intermenstrual bleeding 24 months after treatment (Additional file 5). An overview of questionnaires and timepoints is shown in Table 1.

**Table 1 Tab1:** Schematic overview of follow up questionnaires for participants

Timepoints	T_0_: Baseline	T_2_: 6 months	T_3_: 12 months	T_4_: 18 months	T_5_: 24 months
1. 6 months follow up questionnaire		x			
2. Women’s satisfaction		x	x		x
3. EQ-5D-5L	x	x	x		x
4. PBAC	x	x	x		x
5. Cyclic pelvic pain and MMAS	x	x	x		x
6. Side-effects or complications		x	x		x
7. iMCQ and iPCQ		x	x	x	x
8. Menstrual calendar					x

EQ-5D-5L = The 5-level EuroQol version of quality-of-life questionnaire, PBAC = Pictorial Blood Loss Assessment Chart, MMAS = menorrhagia multi-attribute scale questionnaire, iMCQ = iMTA Medical Consumption Questionnaire, iPCQ = iMTA Productivity Cost Questionnaire

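### The quality-of-life and PBAC model is specified as GEE with a participant random effect, which names two different models that handle missing data differently

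*Protocol article*

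**What the plan says.** All of this is in the protocol article.

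- **Model** (Data-analysis): quality of life and longitudinal PBAC scores are to be analysed with "Generalized Estimating Equations with treatment group, time, and treatment group—time interaction as variables, and a random effect for participants".
- **Baseline** (Data-analysis): EQ-5D and MMAS are to be presented "with the baseline values adjusted for".
- **Missing quality-of-life data** (Data-analysis): "Quality-of-life data will be modelled using techniques that allow for missing data".
- **Other questionnaire outcomes** (Data-analysis): "For remaining secondary outcomes measured using questionnaires, multiple imputation will be considered if necessary".
- **Visits** (Questionnaires for participants): "At 6-, 12- and 24-months participants will receive a questionnaire containing the MMAS questionnaire, the EQ-5D-5L questionnaire, and PBAC scoring". MMAS, EQ-5D-5L and PBAC are also measured at baseline.
- **Software** (Data-analysis): "The analysis will be done using the software Statistical Package for the Social Sciences".

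The Sample size section plans for 10% loss to follow-up.

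**The concern.** GEE is a marginal method. It models the population mean, treats within-woman dependence through a working correlation, and uses robust standard errors. A participant random effect defines a different, conditional model: a linear or generalised linear mixed model fitted by likelihood. A reader cannot tell from the sentence which of the two will be fitted.

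The two part company on missing data. Quality of life is set apart from the outcomes for which imputation may be considered, so its model is the only missing-data strategy that the article states. PBAC is less clear: it shares the model sentence but could count among the remaining questionnaire outcomes.

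Score-related dropout is plausible. The Background says that about one in five women is dissatisfied after ablation and seeks further treatment, and the Interventions section describes no sham device for controls. That dropout will follow earlier scores is an inference, not something that the article states. What is at stake is the treatment contrast on MMAS, EQ-5D-5L and PBAC.

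**Working it through.** **1. The plan's own design figure.** Inputs from the Sample size section: 15% against 8%, two-sided alpha 0.05, power 80%, unpooled variance, 10% loss.

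n per arm = (z₀.₉₇₅ + z₀.₈₀)² × [p₁(1−p₁) + p₂(1−p₂)] / (p₁−p₂)²
= 7.849 × (0.1275 + 0.0736) / 0.0049 = 322.1, so 323 per arm and 646 in total.
646 / 0.90 = 717.8, so 718.

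Both stated figures reproduce. They concern hysterectomy and do not depend on the longitudinal model.

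**2. The two models side by side.**

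| | GEE | Mixed model |
|---|---|---|
| Within-woman dependence | working correlation | random effect or covariance structure |
| Participant random effect | none | yes |
| Estimation | estimating equations, robust SE | ML or REML |
| Valid without weighting or imputation | in general, if missingness is completely at random or depends only on model covariates | under MAR, if correctly specified |

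The sentence takes its name from the first column and its random effect from the second.

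**3. Why the working correlation decides the bias.** With treatment, time and their interaction in the model and an independence structure, the 24-month contrast is essentially the baseline-adjusted difference among women still observed at 24 months. Scores at 6 and 12 months from women who later drop out do almost nothing to correct it. With a structure close to the true correlation, those scores do contribute, and for a continuous outcome with identity link the estimate moves close to the likelihood answer.

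**4. Illustration A, in MMAS points.** All inputs are assumptions except the 323 per arm: SD 25, AR correlation 0.7, baseline plus three visits, dropout dependent on the previous score in the control arm only, 24-28% missing at 24 months, true effect 0, 60 simulated trials, Monte Carlo SE about 0.27.

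| Model | Mean 24-month effect (truth 0) |
|---|---|
| GEE, independence | −2.33 |
| GEE, exchangeable | +0.67 |
| Random-intercept mixed model | +0.66 |

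In SD units the first is −2.33 / 25 = −0.09. The other two cannot be told apart. Both are about 2.5 Monte Carlo SEs from 0 (0.67 / 0.27), as expected when a random intercept or exchangeable structure is imposed on AR data.

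**5. Illustration B, in SD units.** Assumed: 646 women, true effect 0.30, about 29% dropout by the last visit, dependent on the last score in opposite directions by arm, 60 simulated trials, Monte Carlo SE about 0.01.

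| True correlation | GEE independence | GEE exchangeable | Random-intercept mixed |
|---|---|---|---|
| Exchangeable 0.6 | 0.15 | 0.30 | 0.31 |
| AR 0.7 | 0.12 | 0.33 | 0.34 |

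Independence loses 0.30 − 0.15 = 0.15 (half) to 0.30 − 0.12 = 0.18 (three fifths) of the effect. Exchangeable GEE again tracks the mixed model.

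**6. At the planned loss.** Illustration A repeated with about 10% missing and assumed dropout slopes (300 simulated trials, Monte Carlo SE 0.12) gives about −1.1 to −1.3 points for independence and about 0.0 to +0.2 for exchangeable. The first is roughly half of −2.33; a gentler dependence of dropout on the score would give less.

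**The case against.** The strongest reply is that this is a slip of wording with little practical harm. Much of that stands.

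- A reader might infer that GEE of any kind would bias these results, or that only a mixed model is valid when dropout follows earlier scores. Neither is supported. Exchangeable GEE matched the mixed model in both illustrations, and weighted GEE or GEE after multiple imputation can also handle MAR. Moreover, a random intercept in a linear model implies an exchangeable correlation, so independence is the structure least in keeping with the sentence.
- A reader might infer that the plan claims validity under MAR. It does not: it speaks only of techniques that allow for missing data. GEE uses the available visits of incomplete participants, so the phrase is not false for GEE. The reliance on robustness is inferred from imputation being kept for the other outcomes.
- A reader might infer that the model will be chosen after the data are seen. The article does not show that. It condenses a fuller protocol, and an analysis plan may settle the choice. An unnamed working correlation or covariance structure is no fault in an article.
- Estimating-equation methods for mixed models do exist in the methods literature, so the combination is not impossible in every sense. The article describes no such variant.
- The 24-29% missingness in the illustrations is assumed. Questionnaire non-response may exceed the planned 10% loss, but no figure in the document says so.

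What does not fall away is the contradiction. The article positively states a model that ordinary GEE cannot contain. That is a wrong statement, not an omitted detail.

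**Conclusion.** The concern holds as a contradiction in the model statement: one sentence names a marginal GEE and a mixed model, and for quality of life that model is the stated means of allowing for missing data.

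The size is conditional. With an independence working correlation and score-dependent dropout, the bias can be material: about −2.3 MMAS points at 24-28% missing, roughly half that at 10%, on an assumed SD of 25, AR correlation of 0.7 and dropout dependent on the score in one arm. With a near-correct working correlation it is negligible or close to that of the mixed model. These figures show what the choice can do; they do not predict this trial.

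A reader might extend the point to the main result. The documents do not support that: the relative risk and chi-squared test for hysterectomy use neither model, and 646 and 718 are unchanged. Only secondary outcomes are affected, so this is a should-fix point.

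**What to change.** **Preferred.** Replace the sentence with a linear mixed model for the 6-, 12- and 24-month scores. Fixed effects: treatment, categorical time, treatment-by-time and baseline score. Use preferably an unstructured within-woman covariance, since a random intercept alone was slightly off under AR correlation. Estimate by REML, state the MAR assumption, transform PBAC as its distribution requires, and delete the reference to GEE.

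**Equally coherent alternative.** Keep GEE, delete the random effect, name a non-independence working correlation, and add multiple imputation or weighting for missing scores.

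Either removes the contradiction. If a separate analysis plan already fixes one of them, align the protocol wording with it before the data are analysed.

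**Cost.** About one sentence of text and no new data. Mixed models can be fitted in SPSS, the software already named. Baseline adjustment of EQ-5D and MMAS and transformation of questionnaire data are already planned.
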